**Fig. 1 Fig1:**
[figure not shown]
Coping with Unusual ExperienceS for 12–18 year olds (CUES+) study design. Key: *UE* Unusual experience, *SDQ* Strengths and Difficulties Questionnaire [41, 42], *TAU* Treatment as usual (routine care)

**Fig. 2 Fig2:**
[figure not shown]
Coping with Unusual ExperienceS for 12–18 year olds (CUES+): schedule of enrolment, interventions and assessments. Key: *UED* unusual experience with distress, *CBT* cognitive behavioural therapy, ^1^Strengths and Difficulties Questionnaire (SDQ), Emotional Problems subscale [41, 42]. ^2^Unusual Experiences Questionnaire (UEQ) – severity score [10, 14, 39]; ^3^from the Development and Wellbeing Scales (DAWBA) [45]. ^4^Child adaptation of the Clinical Service Receipt Inventory [51]; ^5^EuroQol Health Questionnaire, youth version (EQ5D-Y) [52–54]. ^6,7^Parent- and child-reported full SDQ and UEQ (including UEQ appraisals [68, 72]; ^8,9^researcher-reported functioning (Child Global Assessment Scale, Health of the Nation Outcome Scales for Children and Adolescents) [86–88];^10–12^child- and parent-reported mood and behaviour (Revised Child Anxiety and Depression Scales [55]; Elevated Mood Scales [56–58]; Me and My School, behavioural problems subscale [59]; ^13–17^child-reported trauma sequelae/emotion regulation (Difficulties in Emotion Regulation Scale [60]; Adolescent Dissociative Experiences Scale [61]; Child Revised Impact of Events Scale-13 [62]; DAWBA eating disorder screen [45]; Maudsley Addiction Profile [63]); ^18^Time budget measure of activities and peer relationships [64–66]; ^19^Beliefs about problems [69–72]; ^20^Brief Core Schema Scale [27, 68]; ^21^Jumping to conclusions reasoning task [26, 73]; ^22–24^Parent caregiving experience and appraisals (Five Minute Speech Sample [74]; Brief Illness Perception Questionnaire [36, 69]; Experience of Caregiving Inventory [78]; ^25–28^parent distress/wellbeing and coping (Patient Health Questionnaire, Generalised Anxiety Disorder, Short Warwick-Edinburgh Mental Well-Being Scale, Brief COPE Scale with Confidante Question [36, 75–78]. ^29–32^Short CHOICE with goals [84]; Session and Outcome Rating Scales [79–82]; service satisfaction [83]; ^33^demographics (age, gender, ethnicity, parent-reported developmental delay); ^34^life events, bullying and brief trauma screen [69.70,45]; ^35-37^Wechsler Intelligence Scales for Children – Fourth Edition (WISC-IV), Individual Attainment Test II (WIAT-II), Abbreviated Scale of Intelligence II (WASI-II) [48–50]. ^38^Children’s Post-Traumatic Cognitions Inventory [44]

### Procedure

#### Recruitment

We will recruit directly from CAMHS community mental health teams, starting in one borough, and extending to the other boroughs as required to maintain the target recruitment rate. Young people presenting with UEDs (according to the screening measure) will be invited by their team to find out more about the study, and, if agreeing, will be contacted by the CUES+ study researcher. The usual consent procedure for participants aged under 16 years will be to secure parental consent and child assent; and for those 16 years and over, to seek the young person’s consent, and parental consent if the child agrees to familial participation. This will be guided by the clinical team’s assessment of the young person’s capacity and other clinical issues impacting on consent (e.g. whether Gillick competences [43] are met, managing parental conflict and split care arrangements). Young people reporting UEDs (and their families where appropriate) will be offered the Information Sheet and Consent/Assent Forms, with a follow-up call from the research team within 2 to 4 weeks. Telephone conversations and meetings will take place as needed to discuss the study; at least 24 h will elapse between receipt of the study information and consent being sought for participation. Consenting young people and their families will be offered a baseline assessment and will be randomised only following completion of this.

#### Ethical approval

The study has been reviewed and given a favourable opinion by the London Hampstead National Research Ethics Service Committee (reference: 14/LO/1970). Approval to recruit for the study in CAMHS in the four boroughs of Southwark, Lambeth, Croydon and Lewisham was granted centrally by the Joint Research and Development Office of the South London and Maudsley NHS Foundation Trust and the Institute of Psychiatry, Psychology and Neuroscience (reference R&D2015/003).

#### Intervention

The therapy will comprise up to 16 sessions, delivered over 16 weeks, including up to 12 sessions of individual CBT, adapted for adolescents, and up to four family support sessions. The intervention will be delivered in addition to routine care (specialist care coordination, practical and emotional support for the young person and their family, and medication as appropriate), and will be compared to routine care alone. After the 24-week assessment, adolescents in the routine care condition will be offered the intervention.

Intervention will not ordinarily exceed a total of 16 sessions (notwithstanding requirements to extend therapy to ensure safety and wellbeing), but may exceed 16 weeks of delivery, as needed to accommodate, for example, holidays and examination periods. The intervention content has been developed from our earlier inpatient protocols for individual and family work with young people with psychosis [32], and adapted for young people with UEDs in the general population [33] and in services for children with emotional and behavioural problems [34]. Pilot work has demonstrated feasibility, acceptability and potential helpfulness of the intervention [32, 33]. Individual work focusses on developing a collaborative understanding of UEDs, together with skills in affect regulation, managing negative automatic thoughts, behavioural tests, dealing with social difficulties and adverse life events, recognising and compensating for cognitive biases, and a section on taking the work forward and preventing future difficulties. Where there has been trauma, therapists complete pre- and post-therapy measures of event appraisals and post-traumatic cognitions to aid therapy [44]. Therapy is tailored to take account of the developmental stage and presenting issues of the child/young person, with an emphasis on identity formation, understanding of the self in relation to the experience of psychosis/UEDs, social inclusion and self-esteem. Therapy materials are designed to be fun, interactive and engaging. Family support is crucial when working with young people, and has been requested by parents consulting on our studies. Family work comprises recognition and understanding of the child’s difficulties, sharing the intervention plan, and troubleshooting any key familial difficulties.

#### Therapists

We will train and supervise CAMHS community therapists to deliver the intervention. Therapists will contribute a full day or half a day per week, depending on the agreement with their service, to see two to four trial cases. The combined caseload across all therapists, given the study recruitment targets, will be a maximum of 24 at any one time, allowing 60 young people to be seen over a year. We will stagger the input of the therapists to accommodate the growing caseload as the study progresses.

Therapists will be trained to competence in delivery of the manualised intervention and closely supervised by the trial coordinator/supervisor. Therapy adherence will be monitored by supervisors on an ongoing basis through audio-recorded therapy sessions (for which we will request service user consent). Adherence to the manual will be checked by internal raters who are not directly involved in the care of the participant (i.e. not therapist or supervisor), using checklists of manual content incorporating general cognitive therapy skills, specific skills in working with UEDs, and appropriate tailoring to the developmental stage and presentation of each young person and family [32, 33]. An independent expert will rate 10% of internally rated sessions: we will consider 90% rated as adherent to be acceptable. For the duration of the trial, we will ensure that trained therapists do not provide care coordination for young people who are allocated to routine care. In each team, there is an early-intervention-in-psychosis liaison worker, who takes responsibility, irrespective of the trial, for ensuring that routine care meets the needs of young people presenting with psychosis.

### Measures

#### Outcomes and timeline

Following informed consent from each participant, all outcomes will be assessed by a trained study researcher. Demographic/clinical characteristics (age, gender, ethnicity, parent-reported developmental delays, family circumstances, diagnoses), brief cognitive functioning (word reading, working memory and general intelligence) and history of adverse life events and bullying will be assessed at baseline [45–50]. Outcomes will be assessed at baseline (0 weeks) then at 16 weeks and 24 weeks post randomisation, irrespective of treatment duration. Assessments will not be completed more than 2 weeks after the planned assessment time point. Outcomes and all measures are listed in Table 1 and will be completed according to the schedule in Fig. 2.

**Table 1 Tab1:** Coping with Unusual ExperienceS for 12–18 year olds (CUES+): list of measures

Measure	Completed	
	By	At
Primary outcome		
1. Strengths and Difficulties Questionnaire-Emotional Problems (SDQ-E) [41, 42]	1	0,1
Main secondary outcomes		
2. Unusual Experiences Questionnaire – severity score (UEQ) [10, 14, 39]	1	0,1
3. Self-harm (Development and Wellbeing Scales, DAWBA) [45]	1	0,1
4. Child Clinical Service Receipt Inventory (CSRI) [51]	2,3	− 1,2
5. EuroQol Health Questionnaire, youth (EQ5D-Y) [52–54]	1,2	0,2
Other secondary child outcomes		
6. Strengths and Difficulties Questionnaire (SDQ) [41, 42]	1,2	0,1,2
7. Unusual Experiences Questionnaire (UEQ) [10, 14, 39]	1,2	0,1,2
8. Child Global Assessment Scale (C-GAS) [86]	3	0,1,2
9. Health of the Nation Outcome Scales for Children and Adolescents (HoNOSCA) [87, 88]	3	0,1,2
10. Revised Child Anxiety and Depression Scales (RCADS) [55]	1,2	0,1,2
11. Elevated Mood Scales [56–58]	1,2	0,1,2
12. Me and My School, behavioural problems (M&MS) [59]	1,2	0,1,2
13. Difficulties in Emotion Regulation Scale (DERS) [60]	1	0,1,2
14. Adolescent Dissociative Experiences Scale (A-DES) [61]	1	0,1,2
15. Child Revised Impact of Events Scale (CRIES-13) [62]	1	0,1,2
16. Eating disorder screen (DAWBA) [45]	1	0,1,2
17. Maudsley Addictions Profile (MAP) [63]	1	0,1,2
18. Time budget of activities and peer relationships [64–66]	1	0,1,2
19. Beliefs about problems (BAP) [69–72]	1	0,1,2
20. Brief Core Schema Scale [27, 68]	1	0,1,2
21. Jumping to conclusions [26, 73]	1	0,1,2
Secondary parent outcomes		
22. Five Minute Speech Sample (FMSS) [74]	2	0,1
23. Brief Illness Perception Questionnaire (BIPQ) [36, 69]	2	0,1
24. Parental Experience of Caregiving Inventory (ECI) [36, 78]	2	0,1
25. Depression: Patient Health Questionnaire (PHQ-9) [75]	2	0,1
26. Generalised Anxiety Disorder (GAD-7) [76]	2	0,1
27. Warwick-Edinburgh Mental Well-Being Scale (WEMWBS) [77]	2	0,1
28. The Brief COPE Scale with Confidante Question [36, 78]	2	0,1
Sessional and satisfaction (therapy only)		
29. Short CHOICE with goals [84]	1,2	3
30 and 31. Session and outcome scales (SRS & ORS) [79–82]	1,2	3
32. Service feedback scales [83]	1,2	2
Baseline only measures		
33. Demographics and developmental history	1–3	0
32. Adverse Life Events, bullying and brief trauma screen [45–47]	1	0
33–35. Word reading, digit span, vocabulary, matrix reasoning [48–50].	1,3	0
Detailed trauma assessment (therapy only)		
36. Children’s Post-Traumatic Cognitions Inventory [44]	1,3	4

Key: Completed by: 1 = child; 2 = parent; 3 = researcher/therapist. Completed at: − 1 = 6 months preceding baseline; 0 = 0 weeks, baseline; 1 = 16 weeks; 2 = 24 weeks; 3 = sessionally; 4 = early in therapy

#### Primary outcome

The primary outcome will be distress at 16 weeks, assessed using the SDQ-E, child-reported [41]. The SDQ is well-validated and routinely used in local services for youth up to 19 years [41, 42].

#### Secondary outcomes

Secondary outcomes will be child-reported UED severity at 16 weeks, assessed using the self-report UEQ [10, 14, 39]. Self-reported self-harm [45] and adverse events including attendance at accident and emergency services, and economic costs, including quality-adjusted life years (QALYs) [51–54] will also be assessed.

#### Other clinical outcomes

We will also measure the cognitive, social, emotional and behavioural therapy targets hypothesised to maintain UEDs. These will be assessed at 0, 16 and 24 weeks. Areas assessed include child self-reported mood and behaviour problems (anxiety, depression, elevated mood, anger, hyperactivity, conduct disorder and peer problems) [41, 42, 55–59]; child-reported trauma sequelae, emotional regulation, substance misuse and eating disorders [45, 60–63]; activity levels, social support and sleep pattern [64–66], appraisals of the self and others, UEDs and the presenting problem [27, 28, 67–72]; and reasoning style [73]. Parent/carer measures will be completed at 0 and 16 weeks, and will include the 5-min speech sample to assess family relationships [74], and measures of parental affect, wellbeing, caregiving experience, and coping [75–79], as well as parental assessments of child mood and behaviour difficulties and UEDs [10, 14, 41, 42, 55–59]. Sessional ratings will be used to measure the therapeutic relationship, therapy progress and overall satisfaction [80–85]. The Child Global Assessment Scale [86] and Health of the Nation Outcome Scale for Children and Adolescents [87, 88] will be completed at the 0-, 16- and 24-week time points to assess general childhood psychopathology and impact on functioning.

#### Economic outcomes

The main outcomes of interest will be unit changes in distress levels measured by the SDQ-E (the primary outcome of the RCT) [41, 42], and the QALY gain as measured with the EQ-5D-Y questionnaire at baseline (0 weeks) and 24-week time points. The EQ-5D-Y is a child version of the EQ-5D, which measures health-related quality of life (HRQoL) in young populations using an age-appropriate adjustment to the wording of the original questionnaire [52–54]. The EQ-5D-Y consists of five domains (mobility, self-care, usual activities (e.g. work, study, housework, family or leisure activities), pain/discomfort and anxiety/depression) and each is rated 1 (no problems), 2 (some problems), or 3 (a lot of problems) [54]. UK values will be applied to the distinct health states derived from the EQ-5D-Y to estimate the utility value for each participant at each time point, and the area-under-the-curve methods will be used to calculate the QALYs [53].

#### Service use and costs

Economic analysis will be conducted from the perspective of the national health care system and personal and social services (NHS and PSS), but a wider perspective including costs borne by the participants and their families will also be considered. Potential costs will include lost education for children and lost time from work for parents. The costs of lost education will be estimated using a notional figure for the value of days in education. Intervention costs will include the time spent by CAMHS community therapists to deliver the intervention, including training and supervision costs. The Client Service Receipt Inventory (CSRI) will be adapted and administered to record participants’ use of health and social services for the 6-month periods before and after baseline, respectively [51]. The CSRI has been developed by members of King’s Health Economics and has been widely used in mental and physical health economic evaluations. The data collected through the CSRI will be used to calculate average service costs and total costs of care. All unit costs will be derived using routine data sources, such as the NHS reference costs [89] and the Unit Costs of Health and Social Care [90], as well as study-specific estimates where appropriate. Medication use, such as name/type of drug, dosage levels and frequencies, will be recorded and costs will be calculated based on prices from the *British National Formulary for Children* [91] and the Prescription Cost Analysis [92]. From these, a mean cost per intervention and a mean cost taking into account participant and carer costs will be estimated.

### Sample size

We will recruit 120 participants, randomly allocating 60 per group. From previous experience, we will allow for a conservative loss-to-follow-up of approximately 33% (85% follow-up achieved in an earlier pilot study [34]. With 45 successfully followed up in each group, we would have 80% power to detect between group differences for the smallest achieved effect sizes from previous studies of cognitive therapy with young people (0.6 SD) using a two-group *t* test with a 0.05 two-sided significance level. We will have 90% power to detect effect sizes of 0.7 SD and above. Our pilot work shows between group effect sizes of 0.6 in inpatients [32]. In practice, the power will be increased by using a mixed (random)-effects model allowing for baseline covariates including distress (rather than a simple *t* test) to gain precision in the effect estimates, but this increase is likely to be counteracted by allowing for modest between-therapist variation.

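### The plan allows for 33% loss but bases power on 45 of 60 per arm, which is 25% loss, so the stated 80% and 90% power do not hold at its own attrition allowance

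*Protocol article*

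**What the plan says.** Everything relevant is in the Sample size section of the protocol article.

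- Recruitment: "We will recruit 120 participants, randomly allocating 60 per group".
- Attrition: "we will allow for a conservative loss-to-follow-up of approximately 33"%. The supporting experience cited beside it is "85% follow-up achieved in an earlier pilot study", that is, 15% loss.
- Power: "With 45 successfully followed up in each group, we would have 80% power to detect between group differences". The effect in question is 0.6 SD, described as the smallest achieved in earlier studies of cognitive therapy with young people. The next sentence adds: "We will have 90% power to detect effect sizes of 0.7 SD and above".
- Test: a two-group t test at the two-sided 0.05 level.

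The section closes by saying that the mixed model should gain precision from baseline covariates, but that between-therapist variation will probably cancel the gain. It quantifies neither.

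**The concern.** Three figures in consecutive sentences cannot all be true: 60 randomised per arm, about a third lost, and 45 retained per arm. Losing a third of 60 leaves 40, and retaining 45 of 60 is a loss of a quarter. The word approximately does not cover a gap of five participants per arm, ten in all. The pilot's follow-up does not explain 45 either, since 85% of 60 is 51.

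The power figures rest on the 45. A reader told that 33% is a conservative allowance will take it that the trial keeps 80% power for 0.6 SD even if a third of participants are lost. If losses did reach that level, a null result on the primary outcome (SDQ-E at 16 weeks) would be judged against a power the design did not have.

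**Working it through.** **Inputs (all from Sample size).** 60 randomised per arm; loss about 33%; 45 followed up per arm; effects of 0.6 and 0.7 SD; two-sided alpha 0.05; two-group t test; pilot follow-up 85%.

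**Step 1. Retention.**
- 60 × (1 − 0.33) = 40.2, so about 40 per arm at the stated loss.
- 45 / 60 = 0.75, so 45 per arm implies 25% loss.
- 60 × 0.85 = 51 per arm at the pilot's follow-up.

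**Step 2. Power formula.** With n per arm and standardised difference d, the t statistic has 2n − 2 degrees of freedom and noncentrality d × √(n/2). Power is the probability that this noncentral t variable falls outside the two-sided 5% critical values. As a hand check, the normal approximation is Φ(d√(n/2) − 1.96).

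**Step 3. Reproduce the stated power at 45 per arm.**
- d = 0.6: noncentrality 0.6 × √22.5 = 2.846; power 80.4% (normal approximation 81.2%).
- d = 0.7: noncentrality 0.7 × √22.5 = 3.320; power 90.7% (normal approximation 91.3%).

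Both stated figures reproduce. The smallest n per arm giving 80% power at 0.6 SD by the t test is exactly 45, so there is no slack at that point.

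**Step 4. Repeat at other retention levels.**

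| Loss | n per arm | Power at 0.6 SD | Power at 0.7 SD |
|---|---|---|---|
| 25% (implied by 45 of 60) | 45 | 80.4% | 90.7% |
| 33% (stated) | 40 | 75.5% | 87.1% |
| 15% (pilot) | 51 | 85.1% | 93.8% |

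At 40 per arm the normal approximation gives 76.5% and 87.9%, so the shortfall does not depend on the choice of formula.

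**Step 5. Detectable effects at 40 per arm.** 0.634 SD with 80% power and 0.734 SD with 90% power. At 45 per arm the corresponding values are 0.597 and 0.691 SD.

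**Step 6. Where 33% may have come from.** 45 × 1.33 = 59.85, about 60. The numbers fit a one-third mark-up on 45, instead of division by the proportion retained. Done correctly, keeping 45 after 33% loss needs 45 / 0.67 = 67.2, so 68 per arm or 136 in total. This origin is inferred from the arithmetic; the document does not state it.

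**The case against.** The strongest reply is that the power sentence is conditional on 45 being followed up, and on that condition it is correct. If 45 was the design target and 60 was reached by adding a third, the only error is the attrition percentage, and both power figures stand once it is changed to 25%. The document does not show which number was intended, so this reading is open, and the fix below allows for it. It does not make the paragraph right as written: the 33% is offered as the allowance behind the 45, and at 33% there are not 45.

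A second reply is that the effect is small and arises only in a pessimistic scenario. Power drops by about five points at 0.6 SD and under four at 0.7 SD. The one observed follow-up rate quoted would give more power than claimed. The Statistical analysis section also lets participants give the primary outcome alone, in person, by telephone or by email, which should help retention. All of that is fair and limits the size of the problem. But an allowance called conservative is there to show that power survives the pessimistic case, and here it does not.

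Third, a null result should be read from the confidence interval and the number actually followed up, not from a planning figure. That is sound practice, and the mismatch does not touch the estimate, the analysis model or the type I error. The power statement is still part of the published case for the sample size and should agree with itself.

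The mixed model does not close the gap, because the section itself expects its gain to be offset by therapist variation.

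**Conclusion.** The point holds: the paragraph is wrong as written. The stated 33% loss and the 45 of 60 retained per arm contradict each other, and nothing else in the article reconciles them. The power calculation is correct for 45 per arm. At the plan's own 33% allowance, power is 75.5% instead of 80% at 0.6 SD and 87.1% instead of 90% at 0.7 SD. The type II error at 0.6 SD is then about 24.5%, not 20%, and the effect detectable with 80% power rises above 0.6 SD to 0.63 SD.

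These figures assume equal loss in both arms, the unadjusted two-group t test that the section names, and no net effect of covariates or therapist clustering, in line with the section's own expectation. If 25% loss was intended, the power figures stand and only the percentage is wrong.

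**What to change.** Make the attrition and power statements agree, leaving the sample size at 120. The sponsor knows which figure was meant and should choose one:

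- **If 45 per arm was the target:** state the loss as about 25%. Power of 80% at 0.6 SD and 90% at 0.7 SD then stands unchanged.
- **If 33% loss was the intended allowance:** state about 40 followed up per arm, with about 75% power at 0.6 SD, 87% at 0.7 SD, and 80% power at 0.63 SD.

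The cost is one corrected sentence. Recruitment, conduct and analysis are unaffected; under the second option the quoted power is slightly less favourable.
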